### Recruitment

Forty therapists, all members of the Deutsche PsychotherapeutenVereinigung (DPtV), working in secondary care will be recruited. All therapists are informed about the study by the DPtV and all interested members are invited to participate in the study. Participating therapists inform their self-referred patients about the study and ask them if there are willing to take part in the present study. Potential study participants (patients) are informed about the possibility of taking part in the present study in the initial therapy session by their therapist. Interested patients receive an information sheet and a written informed consent form by the therapists and are invited to ask questions. After returning the completed informed consent form individually to the therapists, participants are asked to complete online screening questionnaires at home to assess whether they fulfill the inclusion criterion of BDI-II-Score > 13.

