### Sample size calculation

Regarding differences between the two active treatment conditions, we want to be able to detect standardized between-groups effects sizes (Cohen’s *d*) of 0.2. Smaller effect sizes are considered to be negligible from a clinical point of view [27]. At an α error level of .05 (two-tailed), a statistical power (1-Beta) of .80, and a correlation between pre- and post-measurements found in our earlier studies, we need to include 800 participants. This sample size calculation is conservative and is based on a current meta-analysis in which a mean effect of *d* = .28 for online depression programs was found [5]. Since in the current study participants in both conditions will receive psychotherapy, a significant reduction of depressive symptoms can also be expected in the control condition. Therefore, a relatively small effect size between conditions, i.e., depression level after three months between *deprexis* plus psychotherapy vs. psychotherapy is expected.

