**Table 1 Tab1:** **Outcome measures**

	**Patients**	**Therapists**
T0 (Baseline)	• Demographic Variables Questionnaire	• Questions regarding the theoretical orientation
	• Depression: BDI-II	ICD-10 diagnoses of the patient
	• Suicidal tendencies: SBQ-R	
	• Web Screening Questionnaire (WSQ)	
	• Anxiety: GAD-7	
	• Somatic symptoms: PHQ-15	
	• Health-related quality of life: SF-12	
	• Questionnaire for the evaluation of psychotherapy courses (FEP-2)	
	• Empowerment: Psychological Empowerment Scale	
6 weeks	Working Alliance Inventory (patient - perspective)	Working Alliance Inventory (therapist - perspective)
12 weeks	Working Alliance Inventory (patient - perspective)	Working Alliance Inventory (therapist - perspective)
T1 (Primary endpoint) 3 months	As baseline, plus:	Assessment of acceptability of treatment in psychotherapy
	• Subjective rating of the treatment course	
	In intervention group: Subjective rating of treatment	
T2 (Secondary endpoint) 6 months	As Baseline, plus:	Assessment of acceptability of treatment in psychotherapy
	• Subjective rating of the treatment course	
	In intervention group: Subjective rating of treatment	

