### Statistical analyses

Primary and secondary outcomes will be conducted on the intention-to-treat (ITT) sample. A linear mixed-model repeated measures ANOVA with time as a within groups factor and treatment condition as a between-groups factor will be used for the main research question. Mixed-model repeated measures ANOVA uses all available data of each subject and does not involve the substitution of missing values [41]. With regard to the process variable, i.e., the quality of the working alliance, we will conduct Pearson correlations of the WAI with residualized change scores on the primary and secondary outcomes.

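### The planned alliance-outcome Pearson correlations ignore nesting in 40 therapists: they mix within- and between-therapist association, and their test is anti-conservative only if alliance and change both vary by therapist

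*Protocol article*

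**What the plan says.** For the working alliance, the Statistical analyses section of the protocol article names one method: "Pearson correlations of the WAI with residualized change scores on the primary and secondary outcomes". It names no therapist term, centring or multilevel version, and it does not say whether the patient-rated WAI, the therapist-rated WAI or both are meant. Table 1 collects both at 6 and 12 weeks, in entries beginning "Working Alliance Inventory (patient - perspective" and "Working Alliance Inventory (therapist - perspective".

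The patients are nested in therapists. Recruitment states: "Forty therapists, all members of the Deutsche PsychotherapeutenVereinigung (DPtV), working in secondary care will be recruited". The Sample size calculation states: "we need to include 800 participants".

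Therapist effects come up in two other places. The Randomization section says that allocating patients within therapists lets the trial control for them. The Discussion promises adjustment for therapist allegiance. The abstract and the Objective section present the alliance work as exploratory.

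**The concern.** A Pearson correlation with its usual test assumes independent pairs. Here each therapist supplies about 20 of the therapist ratings, and every patient rating concerns one of the same 40 people. The pooled coefficient therefore combines two different quantities: whether a patient with a better alliance than the therapist's other patients improves more, and whether therapists with better average alliances have patients who improve more.

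The two statements about therapist effects do not help. Randomization within therapists balances therapists between arms, but WAI scores are not randomized. Allegiance is a covariate, not therapist identity, and a plain correlation has no place for it.

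At stake is how the alliance result is read. The coefficient can understate a link within therapists, or show one that exists only between therapists, and its p-value can be too small under conditions that the plan does not check.

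**Working it through.** **Inputs from the document.** N = 800 (Sample size calculation) and J = 40 therapists (Recruitment), so m = 800/40 = 20 patients per therapist on average. The document gives no figure for the correlation itself. Its N is reproduced: for d = 0.2, two-sided alpha 0.05 and power 0.80, n per arm = 2 × (1.960 + 0.842)² / 0.2² ≈ 392.4, so 393 per arm and 786 in total, within 2% of 800. N enters below only as an input.

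**Assumed inputs.** ICC_W (share of WAI variance lying between therapists) from 0.05 to 0.5, ICC_C (the same for residualized change) from 0 to 0.10, equal caseloads and complete data.

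**1. Test with no association at either level.** The variance of the pooled r is inflated by 1 + (m − 1) × ICC_W × ICC_C, and the true type I error is 2 × [1 − Φ(1.96/√inflation)].

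- ICCs 0.3 and 0.05: inflation 1 + 19 × 0.3 × 0.05 = 1.285; 1.96/√1.285 = 1.73; error 8.4%.
- ICCs 0.5 and 0.10: inflation 1 + 19 × 0.5 × 0.10 = 1.95; 1.96/√1.95 = 1.40; error 16.1%.

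Type I error by formula, m = 20:

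| ICC_W | ICC_C = 0 | 0.02 | 0.05 | 0.10 |
|---|---|---|---|---|
| 0.05 | 5.0% | 5.2% | 5.6% | 6.1% |
| 0.1 | 5.0% | 5.4% | 6.1% | 7.2% |
| 0.3 | 5.0% | 6.3% | 8.4% | 11.8% |
| 0.5 | 5.0% | 7.2% | 10.7% | 16.1% |

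Simulation (40 × 20, 3,000 runs each) gives 5.3% at ICCs 0.3/0, 5.5% at 0.1/0.05, 8.2% at 0.3/0.05, 11.1% at 0.5/0.05 and 16.3% at 0.5/0.10. If only 14 patients per therapist had data (an assumption), the formula gives 7.3% at 0.3/0.05 and 12.7% at 0.5/0.10.

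**2. Size of the coefficient.** With r_w the within-therapist and r_b the between-therapist correlation, pooled r ≈ r_w √[(1 − ICC_W)(1 − ICC_C)] + r_b √(ICC_W × ICC_C).

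- *Rating style unrelated to outcome* (r_b = 0, r_w = 0.25, ICC_C = 0.05). ICC_W = 0.3: 0.25 × √(0.7 × 0.95) = 0.204, simulated 0.205. ICC_W = 0.5: 0.25 × √(0.5 × 0.95) = 0.172, simulated 0.174.
- *Effect on power* (r_b = 0, r_w = 0.10, ICC_C = 0). The pooled test has simulated power of 66% at ICC_W = 0.3 and 54% at 0.5, against 79% for the within-therapist test. The p-values become larger, not smaller.
- *Related therapist-level parts* (r_b = ±0.5, r_w = 0, ICCs 0.3/0.05). ±0.5 × √(0.3 × 0.05) = ±0.061, simulated ±0.06 and significant in 40–41% of runs.

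**3. Same data, therapist-centred.** Subtract each therapist's mean from both variables and test on N − 40 − 1 = 759 degrees of freedom. Type I error was 4.9–5.4% in every scenario with no within-therapist link, and an r_w of 0.25 was recovered as 0.25.

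**The case against.** A reader might infer that each therapist's rating habit biases the correlation and makes its p-value too small. The document does not support that, for three reasons.

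- A rating habit belongs to the therapist-rated WAI. The patient-rated WAI can share a therapist-level component, but that is not a rating habit.
- The BDI-II is a patient self-report, so a therapist's leniency on the WAI does not enter it. With no therapist variance in change, type I error stays at 5% whatever the WAI ICC, and a true r is pulled toward zero.
- The p-value is too small only if change scores also vary by therapist, and the document has no figure on that.

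Nor does the protocol say that the within-therapist association is its target. The alliance questions that it states concern whether the combination affects the alliance. Those are comparisons between arms, and this correlation does not answer them. If therapists who build better alliances also get better outcomes, that is a real part of the overall association, so it is too strong to call the pooled value simply biased. The 40% figure also needs an assumed therapist-level correlation of 0.5, and even then r is 0.06, which is less than 0.4% of variance (0.06² = 0.0036).

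Finally, the analysis is exploratory, with no alpha level or decision attached, and details may sit in an analysis plan not shown here.

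All of this limits the point but does not remove it. The article does not leave the method open: it names one that assumes independence, in a design where patients are nested in therapists.

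**Conclusion.** The point holds in a limited form. The named correlation ignores the nesting and yields a coefficient that cannot be assigned to either level. Therapist rating style unrelated to outcome attenuates it, from 0.25 to about 0.21 or 0.17 at WAI ICCs of 0.3 or 0.5. Its test ranges from exact (5%) when change does not vary by therapist, through about 8% at ICCs of 0.3 and 0.05, to about 16% at 0.5 and 0.10. If therapist-level alliance and outcome are related, the pooled r can be significant with no link within therapists.

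All these sizes rest on assumed ICCs, equal caseloads of 20 and complete data. A reader might extend the criticism to the main result, but the BDI-II comparison is randomized within therapists, and neither it nor the sample size of 800 depends on this correlation. The point is minor: a cheap improvement.

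**What to change.** Replace the pooled Pearson correlation with one of two analyses:

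- a therapist-centred correlation of WAI with residualized change, tested on N − 40 − 1 degrees of freedom; or
- a regression of the follow-up score on its baseline value, with a random intercept for therapist and the WAI split into the therapist's mean and the patient's deviation from that mean.

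Report the within- and between-therapist associations separately, for the patient-rated and the therapist-rated WAI, and say which rating each result uses.

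The cost is a few lines of analysis text and about 40 degrees of freedom. With complete data the interval for the within-therapist correlation widens by about √(798/759) − 1 = 2.5%. The between-therapist estimate rests on only 40 therapists and will be imprecise. No new data are needed, because therapist identity is known from the randomization. The Trial status section reports 28 of 800 patients recruited, so at that stage the change could be made before outcome data were analysed.

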## Discussion

Major depression is a prevalent and debilitating disorder. Even though there is ample evidence for the efficiency and effectiveness of (guided) Internet-based interventions as well as for conventional psychotherapeutic treatments for depression, there are various strengths and limitations for both forms of treatments [11].

In this study, we will examine the effectiveness of psychotherapy plus a web-based online depression program (*deprexis*) versus traditional psychotherapy in routine care. We expect that depression levels of participants in the intervention group will be significantly lower after three months and after six months compared to the control group. Additionally, we will gain valuable experiences in combining an online psychological intervention with routine psychotherapeutic care.

A major strength of this study is that to the best of our knowledge, it will be the first study that tests whether an adjunctive web-based treatment tool in psychotherapy for depression can be successfully integrated in routine care and whether the combination will show additional effects compared to a regular psychotherapy for depression.

There are important limitations in the present study that should be mentioned: First, we adopted a crossed therapist design, i.e., a given therapist delivers the control as well as the experimental condition. This design is associated with potential drawbacks [42] but was necessary to choose in order to be able to run the study in routine care. In order to adjust for the potential downsides of this design, in the analyses we will control for therapist allegiance. Second, we will not have standardized assessments of depression diagnosis but rely solely on clinical diagnoses of experienced, licensed psychotherapists plus an online self-report diagnostic assessment. Third, in the present study, we will use *deprexis* as the only adjunctive web-based intervention tool. Therefore, generalizability of the results to other web-based interventions will be restricted.

In addition to the main analysis described in the methods section, our study will be able to address a number of other important research questions, some of which have not been addressed before. For example, we will be able to assess whether an adjunctive web-based treatment affects working alliance scores. Furthermore, we will assess attitudes towards blended psychological interventions from the patients’ as well as the therapists’ perspective.

If leading to a larger improvement, using effective web-based programs such as deprexis as an adjunctive treatment tool could be an interesting option to consider in future mental health care. Additionally, this study will also give first impressions whether blending face-to-face psychotherapy with a web-based adjunct will have negative side effects, i.e., symptom deterioration or decrease of the patient rated quality of the therapeutic alliance. In general, results of this study will provide an informative basis whether a combination of traditional face-to-face psychotherapy and web-based depression program is feasible and whether it is more effective compared to regular psychotherapeutic treatment in depressed outpatients in routine care.

